### 2.5. Sample Size Calculation

According to a prior study [10], AF recurrence rate in the active acupuncture group is expected to be 35.3% and 69.2% in the sham acupuncture group. For 5% significance and 80% power (two-tailed), 33 participants were required for each group. Assuming a dropout rate of 20%, a total of 80 participants with 40 in each group were required.

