### 2.2. Randomization and Blinding

Randomization will be performed using a computer-generated random number list with a permuted block design in a 1 : 1 ratio. Adequate allocation blinding will be ensured by this procedure. After obtaining participant consent, allocation information will be sent to the main investigator at Kyung Hee University Hospital by telephone, and allocations will not be known by the participants or enrolling investigators.

It is almost impossible to blind practitioners due to the nature of the acupuncture intervention; thus they are aware of treatment allocation. Active and sham acupuncture interventions will be conducted as similarly as possible in order to maintain participant blinding. Outcome assessors and statisticians who perform data collection and analysis will all be blinded to participant treatment allocation status. Throughout the study, communications regarding the treatment process will be prohibited.

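### The dropout allowance misses its own target: 20% loss from 40 per group leaves 32, one below the 33 the plan says it needs (minor; wrong as written)

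*Protocol article*

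**What the plan says.** All the figures stand in section 2.5 of the protocol article. The assumed event rates come from a prior study: "AF recurrence rate in the active acupuncture group is expected to be 35.3% and 69.2% in the sham acupuncture group". The error rates are given as "For 5% significance and 80% power (two-tailed"), and the result is that "33 participants were required for each group". The enrolled number follows in the next sentence: "Assuming a dropout rate of 20%, a total of 80 participants with 40 in each group were required". Allocation is equal (section 2.2, "permuted block design in a 1 : 1 ratio"). The abstract and section 2.1 repeat the total of 80. Nowhere else does the article give a different dropout rate or a different evaluable target.

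**The concern.** A dropout allowance has one job: after the assumed loss, the required number of evaluable participants must remain. Here it does not. A reader who takes 20% off 40 gets 32, although the sentence before it requires 33.

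At stake is the internal consistency of the sample size justification. The article states a wrong number, so this is not detail that could be left to a fuller protocol or an analysis plan.

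**Working it through.** **Inputs**, all from section 2.5 except the allocation ratio (section 2.2): recurrence 35.3% (active) and 69.2% (sham); two-sided 5%; power 80%; 33 evaluable per group; 20% dropout; 40 enrolled per group; 1:1 allocation.

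**Step 1: reproduce the 33.** Use the two-proportion formula with pooled variance under the null and no continuity correction, where p̄ = (0.353 + 0.692)/2 = 0.5225 and the difference is 0.692 − 0.353 = 0.339:

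n = [1.96 × √(2 × 0.5225 × 0.4775) + 0.8416 × √(0.353 × 0.647 + 0.692 × 0.308)]² / 0.339² = 32.88, so 33 per group.

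This matches the plan. The arcsine formula gives 32.7, also 33. The evaluable target is therefore sound.

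**Step 2: inflate for 20% loss.**

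- Dividing by the fraction retained: 33 / 0.80 = 41.25, so 42 per group and 84 in total. Check: 42 × 0.80 = 33.6, which meets 33.
- Multiplying by one plus the loss: 33 × 1.20 = 39.6, so 40 per group and 80 in total. This is the stated figure.

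**Step 3: see whether rounding rescues the 40.**

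- Unrounded target: 32.88 / 0.80 = 41.1, still above 40.
- Inflating the total: 66 / 0.80 = 82.5, so 83, or 84 with equal groups.
- Dividing by 0.80 gives 40 only from a target of 32, and the plan says 33.

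**Step 4: what 40 per group delivers.**

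- At 20% loss: 40 × 0.80 = 32 per group.
- Largest loss that keeps 33: 1 − 33/40 = 17.5%.

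**Step 5: the effect on power**, by the formula of step 1:

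| Evaluable per group | Power |
|---|---|
| 33 | 80.2% |
| 32 | 78.9% |

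The loss is 80.2 − 78.9 = 1.3 percentage points, which puts power 1.1 points below the 80% target. Full binomial enumeration for the uncorrected chi-squared test gives 81.4% at 32 per group and 83.3% at 33.

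**The case against.** The strongest case on the other side is that nothing of substance turns on this. One evaluable participant per group is missing, approximate power stays within about a point of 80%, and the exact power of the uncorrected chi-squared test is still above 80% at 32 per group. That stands as an argument about weight, and it is why the point is minor. It does not make the sentence right: the plan sets its target as a count of 33, and 40 with 20% loss does not reach it. The exact figure is also no reason to leave the text alone, because exact power moves unevenly with n (80.1% at 34 per group, below the value at 32).

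It is also fair to say that the article does not show the inflation step. Multiplication by 1.2 is an inference from the fact that 39.6 rounds to 40. The mismatch between 32 and 33 does not depend on it.

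Two stronger readings may tempt a reader, and the documents support neither.

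- *Failed cardioversion adds a further loss on top of the 20%.* Section 2.1 has patients who do not convert dropped from the study, after randomization. Section 2.5 does not say that these patients lie outside its dropout rate, and being dropped reads naturally as part of dropout. The article gives no failure rate from which an extra loss could be computed.
- *Power is well below 80% because Fisher's exact test may be used.* Section 2.6 allows the chi-squared or Fisher's test as appropriate. At 32 per group the expected cell counts are 32 × 0.5225 = 16.7 and 32 × 0.4775 = 15.3, so small counts would not normally call for Fisher's test. Its lower power would also fall short of 80% at the stated 33, so the inflation error does not cause it.

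**Conclusion.** Wrong as written; minor. At its own 20% dropout rate, the stated enrolment of 40 per group yields 32 evaluable, not 33. By the formula that reproduces the plan's 33, power is 78.9% rather than 80.2%. The total consistent with 33 evaluable and 20% loss is 84, four more than stated.

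This rests on the plan's own event rates, on loss falling equally in the two groups, and on the 20% being the whole of the planned loss. It does not show that the trial is materially underpowered, and it does not call the 33 into question.

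**What to change.** Keep 80 participants and restate the sentence in section 2.5 in one of two ways:

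- 40 per group retains the required 33 evaluable provided that loss is no more than 17.5%; or
- with 20% loss, 40 per group leaves 32 evaluable and about 79% power under the stated assumptions.

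If the sponsor prefers to keep both the 33 and the 20%, the enrolment figure that goes with them is 42 per group, 84 in total.

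Either restatement costs one sentence and no extra enrolment, and changes nothing in conduct or analysis. The first states a lower tolerated dropout rate, and the second a slightly lower power. Only the 84 option would add participants, four in all, and would require the total in the abstract and section 2.1 to be changed too.

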### 2.6. Statistical Analysis

Demographic data will be analyzed to identify pretreatment equivalencies and differences between the two groups. Continuous variables will be presented as mean ± standard deviation (SD), evaluated for distribution normalcy, and compared using the Student's *t*-test or Mann-Whitney test wherever appropriate. Categorical variables will be presented as frequencies and percentages and compared using chi-squared or Fisher's exact tests wherever appropriate. AF recurrence during the 12-week follow-up will be analyzed with Kaplan-Meier curves.

Multivariate Cox regression analysis will be performed to determine which factor is most strongly associated with AF recurrence. Serious adverse events will be tabulated per treatment group and analyzed using the chi-squared test.

A *P* value less than 0.05 will be considered statistically significant. All analyses will be performed with SPSS software (Windows version 17.0, Chicago, Illinois, USA) by a statistician blinded to participant allocation.

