## 2. Methods/Design

### 2.1. Patient Population and Study Design

This acupuncture in persistent AF (ACU-AF) study will be a multicenter, prospective, participant and assessor blinded, randomized, sham-controlled clinical trial with 2 parallel arms. Two institutes will take part in this study: Kyung Hee University Medical Center and Kangdong Kyung Hee University Hospital. Eighty patients will be enrolled for 2 years. We will compare the efficacy of active acupuncture and sham acupuncture treatments.

Inclusion and exclusion criteria are listed in Table 1. Flow diagram is displayed in Figure 1. The following data will be evaluated at baseline: demographic data, electrocardiographic and echocardiographic data, comorbidities, biomarkers, medications, and CHA2DS2-VASc score. AAD (flecainide 75 mg twice daily) will be administered to patients confirmed with persistent AF lasting more than 7 days. Flecainide administration will be initiated 2 weeks before EC and maintained during the follow-up period. The resistance for flecainide is defined as AF is not converted to sinus rhythm with oral flecainide before EC. Other types of AADs are not allowed, so participants taking other drugs will be required to change their medication to flecainide. Heart rate control drugs will be permitted (calcium channel blockers such as verapamil or diltiazem, except digoxin and beta blocker), and all dose increases or decreases will be determined by an attending physician. Simultaneous anticoagulation therapy with warfarin will be performed to achieve the target international normalized ratio (INR) of prothrombin time (range 2-3) before EC and during the follow-up period. Patients resistant to drug therapy will be randomized into active and sham acupuncture groups through central randomization. After randomization, once-per-week active or sham acupuncture will be initiated 2 weeks before EC.

Transesophageal echocardiography (TEE) will be conducted just before EC to rule out atrial thrombus and evaluate heart function. If any thrombus is present, EC will be delayed for 2 weeks. In this event, TEE will be conducted again after continuous warfarin administration for 2 weeks. If the thrombus disappears in that time, or is not present, EC will be performed.

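### The stated between-arm comparison of AF recurrence is unadjusted although likely prognostic baseline data are collected, and non-significant baseline tests cannot show that the arms are equivalent

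*Protocol article*

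**What the plan says.** Section 2.6 opens with the baseline comparison: "Demographic data will be analyzed to identify pretreatment equivalencies and differences between the two groups". Continuous variables are "evaluated for distribution normalcy, and compared using the Student's *t*-test or Mann-Whitney test wherever appropriate" and categorical variables are "compared using chi-squared or Fisher's exact tests wherever appropriate". One threshold covers everything: "A *P* value less than 0.05 will be considered statistically significant". No equivalence margin and no limit on a standardised difference is given.

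For the primary endpoint the section states: "AF recurrence during the 12-week follow-up will be analyzed with Kaplan-Meier curves". No covariate is named. The multivariable Cox model in the same section is there to find which factor is most strongly associated with recurrence. Sections 2.4.2 and 3 (Discussion) both describe that search as irrespective of active or sham treatment.

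The material for an adjusted comparison is already collected. Section 2.1 says: "The following data will be evaluated at baseline: demographic data, electrocardiographic and echocardiographic data, comorbidities, biomarkers, medications, and CHA2DS2-VASc score". Section 2.4.2 lists the same items as candidate factors for recurrence.

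**The concern.** There are two linked weaknesses.

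First, the plan collects variables that it regards as possible drivers of recurrence but leaves them out of the stated comparison of the arms. In a time-to-event analysis, omitting a prognostic factor costs power. It also leaves the estimate exposed to whatever imbalance chance produces in 80 patients.

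Second, the plan aims to identify equivalencies, and the only tools it gives are tests of difference. With no margin stated, equivalence can in practice only mean P of 0.05 or more, which shows nothing of the kind in a sample this small. How far an imbalance distorts the result depends on its size and on the prognostic strength of the factor, not on its P value.

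**Working it through.** **Inputs from the protocol article.** Section 2.5 plans on recurrence of 69.2% under sham and 35.3% under active treatment, and gives the size before dropout as follows: "For 5% significance and 80% power (two-tailed), 33 participants were required for each group". The randomised number is 40 per arm. Section 2.6 sets significance at P<0.05.

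**1. The plan's own figure.** Pooled two-proportion formula, mean rate (0.353 + 0.692)/2 = 0.5225:

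n = [1.96·√(2·0.5225·0.4775) + 0.8416·√(0.353·0.647 + 0.692·0.308)]² / 0.339² = (1.3845 + 0.5592)² / 0.1149 = 32.9, so 33 per arm. The stated figure reproduces (power at 33 is 80.2%). It is a power for an unadjusted comparison.

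**2. What a baseline test passes as non-significant.** Largest non-significant observed difference at 40 per arm: t(0.975, 78)·√(2/40) = 1.991 × 0.2236 = 0.445 SD. At 33 per arm it is 0.492 SD. Under randomisation an observed standardised difference has a standard error of about 0.2236. The chance that one given factor falls between 0.3 and 0.445 SD, in either direction, is therefore 2·[Φ(1.99) − Φ(1.34)], about 13%.

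**3. What such an imbalance can do in one trial.** Simulated Cox comparison: 40 per arm, about 53 to 55% events (the planning rates average 52%), no treatment effect, imbalance fixed at 0.4 SD. The HR per SD of the factor is an assumption.

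| Assumed HR per SD | Unadjusted HR | Conditional error | Adjusted HR | Conditional error |
|---|---|---|---|---|
| 1.5 | 1.17 | 6% | 1.00 | 4% |
| 2.0 | 1.28 | 10% | 1.00 | 6% |

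As a rough check, 1.5^0.4 = 1.18 and 2.0^0.4 = 1.32; the simulated values lie at or a little below these. A second simulation gave unadjusted HRs of 1.17 to 1.27 and a conditional error of about 8%. Averaged over random imbalances, the unadjusted error was 4.9% to 5.1%.

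**4. Power forgone.** Assumed treatment HR 0.45, chance imbalance only, adjusting for one factor. Three separate simulations gave:

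| Assumed HR per SD | Unadjusted to adjusted power | Gain (points) |
|---|---|---|
| 1.5 | 68% to 73%; 71% to 76%; 71% to 73% | 2 to 5 |
| 2.0 | 62% to 74%; 58% to 73%; 60% to 74% | 12 to 15 |

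The first simulation used 2,500 trials per scenario, so each power has a Monte Carlo standard error of about √(0.7·0.3/2500) = 0.9 points. The small gain at 1.5 is known only roughly.

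Under proportional hazards the planning rates imply a treatment HR of ln(0.647)/ln(0.308) = 0.37, stronger than the assumed 0.45. If that effect were real, power would be higher under either analysis.

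**5. Can the data carry the model?** Expected events are 80 × 0.5225 = 41.8, or 66 × 0.5225 = 34.5 with 33 per arm. Arm plus two factors is three terms: 41.8/3 = 13.9 or 34.5/3 = 11.5 events per term. One or two factors is feasible; a long list is not.

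**The case against.** The strongest reply is that an unadjusted comparison in a 1:1 randomised trial is legitimate. It holds its 5% error on average over randomisations, and adjustment is an efficiency choice whose value rests on assumed prognostic strength. That stands, and it limits the size of the point. So does the rarity of the scenario in step 3. For one factor, chance gives a difference of 0.4 SD or more about 7% of the time, and one between 0.40 and 0.445 SD about 3% of the time, split across both directions.

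It can also be said that covariates are usually named in an analysis plan, which is not shown here, and that the Cox sentence does not expressly exclude an arm term. Both are fair. However, the article describes the Cox model as a search for recurrence factors irrespective of arm, and its stated comparison of the arms carries no covariate. If the chi-squared or Fisher test were also applied to the recurrence proportion, that would be unadjusted too.

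The equivalencies sentence speaks of demographic data. Echocardiographic data and biomarkers are listed separately elsewhere, so applying it to left atrial volume is inference. The sentences on tests are general.

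A reader might infer three stronger things, none of which the article supports:

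- **That the baseline tests often miss a large imbalance.** The type II error of a t-test concerns a true population difference, which randomisation makes zero. The observed imbalance is what matters. An observed 0.5-SD difference at 40 per arm gives t = 0.5/0.2236 = 2.24 and p = 0.028, so it is always flagged. Likewise, an observed 12/40 against 20/40 has a single fixed chi-squared p of about 0.07, not a miss rate.
- **That a non-significant baseline test is what leaves an imbalance uncorrected.** No section ties adjustment to those tests; as written, the comparison is unadjusted whatever they show.
- **That the treatment comparison is biased by design.** Covariate omission does not make it so.

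**Conclusion.** The point holds as an inexpensive improvement, not as a flaw that invalidates the primary analysis. The stated comparison of the arms ignores baseline data that the plan itself treats as possible predictors. The aim of identifying equivalencies cannot be met by the tests given, because at 40 per arm they pass any observed difference up to about 0.445 SD.

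The cost is roughly 2 to 15 percentage points of power, plus exposure to chance imbalance in the single trial. The range rests on assumptions that are not in the article: one factor with an HR of 1.5 to 2.0 per SD, a treatment HR of 0.45, and exponential event times. A weaker factor would bring less. Removing the baseline P values would by itself change no trial result; the gain comes from the adjusted model.

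The statement that the unadjusted test is valid on average applies to arms compared as randomised. Section 2.1 also drops patients whom cardioversion does not convert, after acupuncture has begun. That is a separate question, and covariate adjustment does not settle it.

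**What to change.** In section 2.6:

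1. Before unblinding, name one or two baseline factors already collected, for example baseline left atrial volume. Compare AF recurrence between arms with a Cox model containing arm plus those factors, whatever their observed balance. Show the Kaplan-Meier curves beside it.
2. Keep the search for recurrence factors as a separate, exploratory model.
3. Describe baseline data by arm with standardised differences. Remove the baseline P values and the reference to equivalencies.

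The cost is a few sentences and one more model on data already collected, with no extra patients or procedures. The small downside is that the hazard ratio becomes conditional on the named factors and is slightly less simple to present than unadjusted curves.

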### 2.3. Intervention

#### 2.3.1. Active Acupuncture Treatment Group

The active acupuncture treatment group will receive two forms of acupuncture: electroacupuncture (EA) and intradermal acupuncture (IDA).

EA treatment consists of 4 acupuncture points (unilateral PC5, PC6, ST36, and ST37, Figure 2) [11]. Disposable, sterile needles (0.20 mm × 30 mm, Dongbang Acupuncture Inc., Boryung, Korea) and a low frequency electrical stimulator (ES-160, ITO, Japan) will be used. Each needle will be inserted to a depth of 2 ± 0.5 cm at a 90-degree angle. Then, the practitioner will rotate the needle several times and induce de-qi (acupuncture-evoked sensations including numbness, heaviness, soreness, or distention). Thereafter, needles will be connected to the pole, and 2 Hz continuous electric current will be applied for 20 minutes. Intensity will be increased until participants feel stimulation but not discomfort, and their muscles twitch slightly.

Four bilateral acupuncture points (HT7 and TF4, the* shen men* points) have been selected for the IDA treatment (Figure 2) [11]. Disposable, sterile, sticker-type needles (0.18 mm × 1.3 mm × 1.5 mm, Dongbang Acupuncture Inc., Boryung, Korea) will be used. Each needle will be applied to a depth of 1 mm at a 90-degree angle. Attached needles will be replaced every visit by practitioners. However, when the needles accidentally fall out (e.g., when washing their hands or face) or the participants feel some discomfort in the acupuncture sites after returning home, participants will be instructed to replace the needles themselves. They will be fully instructed by the practitioners on how to replace the needles on their first visit. Even if the needles do not fall out and the acupuncture sites are not uncomfortable, practitioners will teach participants to replace the needles every two days to prevent infection. Participants also will be taught that repetitive stimulation of manual pressure is helpful.

Acupuncture treatments will be conducted by Doctors of Korean Medicine educated by the College of Korean Medicine for 6 years who are licensed by the Korean Ministry of Health and Welfare and who have more than 3 years of clinical experience. All practitioners will be trained to follow the study protocol.

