### 2.7. Safety and Adverse Event (AE) Outcomes

Safety and adverse event (AE) outcomes are defined as any unexpected or unfavorable symptoms, signs, or diseases that occur during or after treatment, which are not necessarily caused by the treatment. These AEs include local pain, hematoma, bleeding, redness, itching, dizziness, or local infection. All participants and practitioners will be taught to report any AEs. If there are AEs, the following items will be recorded by practitioners at each visit, and appropriate actions will be taken: type of AE(s), occurrence date, lost date, frequency of occurrence, severity, strength of association with the treatment, acupuncture intervention actions taken, and actions taken with respect to the participant. Serious AEs, such as death or life-threatening events which require urgent intervention, will be reported to the principal investigators immediately, who will determine whether the participants will be dropped from the study.

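### The statistical section commits to a by-arm analysis of serious adverse events only, although the safety outcome is any adverse event and most of the events listed will rarely be serious

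*Protocol article*

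**What the plan says.** Section 2.7 sets a broad safety outcome: "Safety and adverse event (AE) outcomes are defined as any unexpected or unfavorable symptoms, signs, or diseases that occur during or after treatment". It gives examples: "These AEs include local pain, hematoma, bleeding, redness, itching, dizziness, or local infection". Recording is equally broad: "If there are AEs, the following items will be recorded by practitioners at each visit, and appropriate actions will be taken". The recorded items include type, dates, frequency, severity and the strength of the link to treatment. Serious events are described by example: "Serious AEs, such as death or life-threatening events which require urgent intervention, will be reported to the principal investigators immediately".

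Section 2.6 has one sentence on AE analysis: "Serious adverse events will be tabulated per treatment group and analyzed using the chi-squared test". Earlier in the same section stands a general rule: "Categorical variables will be presented as frequencies and percentages and compared using chi-squared or Fisher's exact tests wherever appropriate". That rule names no variables.

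On the treatments, section 2.3.1 says of the active electroacupuncture needles: "Each needle will be inserted to a depth of 2 ± 0.5 cm at a 90-degree angle". They are then rotated and receive a 2 Hz current for 20 minutes. Under section 2.3.2 the sham electroacupuncture needles go to 0.5 cm, without manipulation or current. The intradermal needles go to 1 mm in both arms. Section 2.1 has warfarin given to an INR of 2-3 before cardioversion and through follow-up.

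**The concern.** The outcome as defined and the analysis as stated do not have the same scope. Section 2.7 collects every AE; the AE sentence in section 2.6 covers only the serious subset. Most of the listed events would enter that analysis only in exceptional cases.

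This matters because electroacupuncture differs between arms in depth, manipulation and current, and the patients are anticoagulated. A difference in bleeding or hematoma is plausible and would interest anyone weighing the treatment. A report that followed the AE sentence literally could state that serious events did not differ and give no by-arm account of the local ones.

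The sentence also names the chi-squared test alone, whereas the general rule allows Fisher's exact test. Serious events are where counts are likely to be smallest.

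**Working it through.** **1. Scope, side by side**

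| Item | Section | Covers |
|---|---|---|
| Safety outcome | 2.7 | Any AE |
| Listed examples | 2.7 | Pain, hematoma, bleeding, redness, itching, dizziness, local infection |
| Recording | 2.7 | All AEs, with severity and relation to treatment |
| Serious AEs | 2.7 | Exemplified by death and life-threatening events |
| Stated AE analysis by arm | 2.6 | Serious AEs, chi-squared test |
| General categorical rule | 2.6 | Variables not named; chi-squared or Fisher |

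No sentence commits to tabulating all AEs by arm, and none excludes it.

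**2. Where the arms differ**

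| Component | Active | Sham |
|---|---|---|
| Electroacupuncture depth | 2 ± 0.5 cm | 0.5 cm |
| Manipulation | Rotation, de-qi | None |
| Current | 2 Hz, 20 min | None |
| Intradermal depth | 1 mm | 1 mm |

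The contrast is confined to electroacupuncture. Participants in both arms get the same instructions for the intradermal needles.

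**3. Information in each comparison**

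The plan gives no AE figure to reproduce. The only input taken from it is 40 patients per arm (section 2.5). All AE rates below are assumptions. Power of the two-sided Fisher exact test at 0.05 is the sum, over all pairs (x, y) with p < 0.05, of Bin(x; 40, p1) × Bin(y; 40, p2).

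| Assumed rates, active vs sham | Expected patients of 40 | Power |
|---|---|---|
| Serious AE, 5% vs 1% | 2 vs 0.4 | 1% |
| Serious AE, 10% vs 2% | 4 vs 0.8 | 11% |
| Local AE, 15% vs 5% | 6 vs 2 | 18% |
| Local AE, 20% vs 5% | 8 vs 2 | 41% |
| Local AE, 30% vs 10% | 12 vs 4 | 53% |
| Local AE, 30% vs 5% | 12 vs 2 | 82% |
| Local AE, 40% vs 10% | 16 vs 4 | 85% |

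If no serious AE occurred in an arm, the exact upper 95% limit for 0 of 40 would be 1 − 0.025^(1/40) = 8.8%. That bounds the rate of serious events and says nothing about local ones.

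**4. The named test with sparse counts**

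Take 4 of 40 vs 0 of 40. The expected count is 2 per arm.

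- Chi-squared, uncorrected: 80 × (4 × 40 − 36 × 0)² / (4 × 76 × 40 × 40) = 2,048,000 / 486,400 = 4.21, so p = 0.040.
- Fisher, two-sided: 2 × C(40,4) / C(80,4) = 2 × 91,390 / 1,581,580 = 0.116.

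The two tests fall on opposite sides of the plan's 0.05 threshold. At 5 vs 0 the values are 0.021 and 0.055, again on opposite sides. At 6 vs 0 they are 0.011 and 0.026, both below it.

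**The case against.** A reader might infer that non-serious harms would never be compared between arms. The documents do not support that. The AE sentence does not say that only serious events will be analyzed, and nothing bars a table of the rest. The general categorical rule names no variables and can hardly be confined to baseline data, because the secondary endpoints have no other named between-arm test; AE type and severity could fall under it too. A fuller protocol or SAP, not shown, may hold the AE tables. All of this stands, and it limits the point to a missing commitment.

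It does not remove the point. The article is not silent on AE analysis: it states one, narrower than its own outcome. If the general rule already governed AEs, the separate sentence with its single test would be unnecessary. An SAP written to match it could carry the restriction forward.

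Three further inferences fail. The contrast in depth, rotation and current does not extend to the intradermal needles, so it gives little ground for expecting infection from those retained needles to differ by arm. Nothing in the documents shows that local harm is the main added risk. Nor can one say that the serious-AE table will be nearly empty: serious events are defined by example, and a bleed needing urgent intervention could be counted there.

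Finally, a fuller table need not settle anything. A split of 6 vs 2 of 40 gives a Fisher p of 0.26. Its main value is descriptive.

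**Conclusion.** The point holds as a mismatch of scope. The safety outcome is any AE, but the only AE analysis expressly committed to by arm concerns serious events, with a test poorly suited to sparse counts. The listed events, bleeding and hematoma above all, are left to a general rule that may or may not be meant for them.

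The size cannot be fixed from the documents. Over the assumed rates, the serious-AE comparison has 1% to 11% power and a local-AE comparison 18% to 85%. These ranges assume 40 evaluable patients per arm and one binary outcome per patient; fewer evaluable patients would generally lower them. The conclusion on scope rests on the text and does not depend on them.

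The change should be made, but it is a correction to the analysis text. Data collection, sample size and the primary analysis are not affected.

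**What to change.** Replace the AE sentence in section 2.6 with:

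*All AEs will be tabulated by treatment group by type, severity and relation to treatment, as patients with at least one event, with bleeding or hematoma shown separately and serious AEs as a subset. Sparse counts will be compared with exact methods (Fisher's exact test or exact 95% CI).*

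If an SAP already specifies such tables, it is enough to bring section 2.6 into line with it. The cost is one sentence and one more table, from data that section 2.7 already has recorded at each visit.
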